## Abstract

**Background:**

Observational cohort studies have suggested that minimally invasive distal pancreatectomy (MIDP) is associated with better short-term outcomes compared with open distal pancreatectomy (ODP), such as less intraoperative blood loss, lower morbidity, shorter length of hospital stay, and reduced total costs. Confounding by indication has probably influenced these findings, given that case-matched studies failed to confirm the superiority of MIDP. This accentuates the need for multicenter randomized controlled trials, which are currently lacking. We hypothesize that time to functional recovery is shorter after MIDP compared with ODP even in an enhanced recovery setting.

**Methods:**

LEOPARD is a randomized controlled, parallel-group, patient-blinded, multicenter, superiority trial in all 17 centers of the Dutch Pancreatic Cancer Group. A total of 102 patients with symptomatic benign, premalignant or malignant disease will be randomly allocated to undergo MIDP or ODP in an enhanced recovery setting. The primary outcome is time (days) to functional recovery, defined as all of the following: independently mobile at the preoperative level, sufficient pain control with oral medication alone, ability to maintain sufficient (i.e. >50%) daily required caloric intake, no intravenous fluid administration and no signs of infection. Secondary outcomes are operative and postoperative outcomes, including clinically relevant complications, mortality, quality of life and costs.

**Discussion:**

The LEOPARD trial is designed to investigate whether MIDP reduces the time to functional recovery compared with ODP in an enhanced recovery setting.

**Trial registration:**

Dutch Trial Register, NTR5188. Registered on 9 April 2015

**Electronic supplementary material:**

The online version of this article (doi:10.1186/s13063-017-1892-9) contains supplementary material, which is available to authorized users.

## Background

Minimally invasive surgery, which includes both laparoscopic and robot-assisted surgery, has undoubtedly been one of the most significant advances in surgery during the past decade and is now the preferred approach for many surgical procedures [1–8]. Minimally invasive surgery aims to reduce postoperative pain and complications and shorten the time to functional recovery [1–8].

Minimally invasive distal pancreatectomy (MIDP) was first described in 1994 by Cuschieri et al. [9] Since then, several observational cohort studies from expert centers have suggested that MIDP is safe, feasible and cost-effective in the treatment of benign, premalignant and malignant lesions of the distal pancreas [10, 11]. These suggestions were confirmed by several systematic reviews of cohort studies that reported reductions in intraoperative blood loss, blood transfusion, complications, wound infections and shorter hospital stay, and an increased rate of spleen preservation, all in favor of the minimally invasive approach [10, 11].

Regarding oncologic parameters, including resection margins and lymph node retrieval, the minimally invasive approach is considered to be at least non-inferior to conventional open distal pancreatectomy (ODP) [12–15]. Case-matched studies, however, have not confirmed the presumed benefits of MIDP [10], indicating that confounding by indication has clearly played a role in the reported results in cohort studies. This is confirmed by a difference in baseline characteristics as reported in many series, such as smaller tumor size in the MIDP group [11]. It is therefore currently unknown whether MIDP, as a routine strategy, actually offers clinically relevant advantages over ODP. Most cohort series were performed in high-volume expert centers, so it is uncertain whether these outcomes of MIDP are generalizable [10]. Hence, randomized controlled trials are needed in order to provide high-quality evidence on the benefits of MIDP over ODP.

Minimally invasive approaches are often assumed to be more expensive than open surgery, because of the need for expensive surgical equipment and sometimes prolonged operative times. However, for several procedures, such as appendectomy, cholecystectomy and colectomy, no difference in overall costs has been demonstrated, mainly because reduced hospital stay balanced the higher procedural costs [16]. The current literature is unclear as to the cost difference between MIDP and ODP [10].

In 2014, the Dutch Pancreatic Cancer Group (DPCG) initiated the longitudinal assessment and realization of minimally invasive pancreatic surgery in The Netherlands (LAELAPS) training program to implement minimally invasive pancreatic surgery in The Netherlands [17]. This program follows the preferred steps of surgical innovation according to the innovation, development, exploration, assessment and long-term study (IDEAL) statement [18–20].

First, a nationwide retrospective analysis on distal pancreatectomy was performed in order to assess the utilization and outcomes of MIDP and ODP [21]. In this retrospective multicenter study in 633 patients, MIDP appeared to be at least non-inferior to ODP, but the nationwide underuse of MIDP (10%) and high conversion rate (38%) revealed clear room for improvement. The subsequent nationwide LAELAPS training program included detailed technique standardization and description, video training and proctoring [17]. In the period after training, there was a sevenfold increase in the use of MIDP, and blood loss and conversion rates decreased even during surgery on more complex tumors, including more pancreatic ductal adenocarcinomas. The 8% conversion rate, 17% Clavien-Dindo grade III or higher complication rate, 6 days hospital stay and 0% 30-day mortality in the period after training were comparable to results from expert centers in the UK and USA [11]. According to the IDEAL framework, a randomized controlled trial should be the next step [18–20]. Accordingly, the aim of the LEOPARD trial is to compare the outcomes, including time to functional recovery, complications, quality of life and costs, after MIDP with ODP within an enhanced recovery setting.

## Methods

### Design

The LEOPARD trial is a randomized controlled, parallel-group, patient-blinded, multicenter, superiority trial investigating the effectiveness of MIDP versus ODP for treatment of symptomatic benign, premalignant or malignant disease of the distal pancreas in an enhanced recovery setting. Eligible patients will be randomized equally to either MIDP or ODP. Splenectomy will be performed only when indicated for oncological or technical reasons.

### Trial population

All adult patients with an indication for elective distal pancreatectomy (with or without splenectomy) because of suspected or proven symptomatic benign, premalignant or malignant disease of the distal pancreas, from 17 centers performing pancreatic surgery in The Netherlands will be assessed for eligibility.

### Inclusion criteria

The inclusion criteria are as follows:Age equal to or above 18 yearsIndication for elective distal pancreatectomy (with or without splenectomy) because of proven or suspected left-sided symptomatic benign, premalignant or malignant diseaseTumor meeting the Yonsei criteria [22] (tumor or cyst confined to the pancreas with an intact posterior pancreatic fascial layer and the tumor located at least 1 cm from the celiac axis)Sufficiently fit to undergo distal pancreatectomy according to the surgeon and anesthetist

### Exclusion criteria

The exclusion criteria are as follows:Tumor or cyst larger than 8 cmSurgical intervention (resection or ablation) of other organs besides the distal pancreas or spleen are required (cholecystectomy is allowed)Previous radiotherapy as treatment of pancreatic cancerChronic pancreatitis (according to the M-ANNHEIM criteria)PregnancyParticipation in another study with interference in study outcomes

### Randomization

Patients will be randomized centrally by the trial coordinators using an online randomization module (ALEA, Clinical Research Unit, Academic Medical Center, Amsterdam, The Netherlands) in a 1:1 ratio between MIDP and ODP, as shown in Fig. 1. Randomization will be stratified by center to balance differences in the surgical procedure and general treatment regimens and by the indication for surgery (malignant versus non-malignant disease). Permuted-block randomization will be used to provide treatment allocation in equal proportions, with block sizes that will be subject to random variation. This will be concealed to all investigators involved in the trial.

**Fig. 1 Fig1:**
[figure not shown]
Minimally invasive versus open distal pancreatectomy for symptomatic benign, premalignant and malignant disease (*LEOPARD*) trial flow diagram according to standard protocol items: recommendations for interventional trials (SPIRIT) [45]. *IC* informed consent, *DP* distal pancreatectomy, *EQ-5D-5 L* Euro-QoL five health dimensions questionnaire, *QLQ-C30* quality of life questionnaire including 30 questions

### Intervention: minimally invasive distal pancreatectomy

Patients are under general anesthesia for minimally invasive distal pancreatectomy, and epidural anesthetic is not mandatory. The patient is placed in a supine position, left side 30 degrees elevated with legs apart. In total, four to five (2 × 12 mm and 2 × 5 mm to 3 × 5 mm) trocars are placed in a semicircular fashion, centered around the supra-umbilical camera. The surgeon stands at the patient’s right side, the assistant controlling the camera stands between the patient’s legs and the assistant surgeon stands at the patient’s left side.

The omental bursa is opened by dividing the gastrocolic ligament using an ultrasonic device (Harmonic ACE® + 7 Shears, Ethicon Inc., Cincinnati, OH, USA), or standard of care. Division of the short gastric arteries depends on the indication of spleen preservation. In patients with spleen-preserving surgery, the left gastro-epiploic artery and short gastric vessels are fully preserved. The posterior fundus of the stomach is retracted. The lesion is identified, either visually or with laparoscopic ultrasound. The splenic artery is identified at the superior margin of the pancreas and slung with a vessel loop which is secured with a Hem-o-lok® clip (Teleflex Medical, [name], Research Triangle Park, NC, USA). Optionally, in spleen-preserving surgery, a laparoscopic bulldog clamp can be placed on the artery to reduce blood loss during the procedure. Transection is postponed until the anatomy (especially the hepatic artery and celiac trunk) is confirmed. Alternatively, the stomach is retracted caudally and the common hepatic artery, celiac trunk and splenic artery are identified cranial to the stomach.

The caudal margin of the pancreas is mobilized and the inferior and superior mesenteric veins are identified. An umbilical tape is placed under the pancreas between the lesion and the spleen and secured with a Hem-o-lok® clip. In the case of suspected malignancy this umbilical tape includes Gerota’s fascia as described previously [23]. The same procedure is performed at the right side of the tumor, potentially over the portomesenteric vein. In the case of malignancy, lymphadenectomy is performed according to the International Study Group on Pancreatic Surgery (ISGPS) consensus [24]. If the tumor is localized in the pancreatic body, lymphadenectomy also involves station 9 (around the celiac trunk).

Dissection according to the radical antegrade modular pancreatosplenectomy (RAMPS) method, as described by Strasberg [25], which includes lymph node dissection from the common hepatic artery to the celiac trunk and splenic artery, is advised in the case of malignancy. The left gastric artery is preserved if possible. In the case of benign and premalignant lesions attempts are made to preserve the spleen. These vessels are either completely spared (Kimura’s technique [26]) or if complete preservation of the splenic vessels is not feasible they will be divided using either Hem-o-lok® clips (at least two clips on the patient’s side) or stapling devices, so the spleen only receives blood via the short gastric arteries (Warshaw’s technique [27]). Splenectomy is performed in the case of gross splenic ischemia. Splenectomy is routinely performed in the case of malignant lesions or risk of malignancy.

The pancreas is divided using an endostapler with the staple cartridge size adapted to the thickness of the pancreas. A graded progressive compression technique is used as described by Asbun et al. [28]. Additional suturing of the pancreatic stump, covering the stump with tissue or a patch, or staple-line reinforcement is allowed. A medial-to-lateral approach is used during the mobilization of the pancreas. The pancreatic tail (with or without the spleen) is put into a leak-proof retrieval bag and extracted using a Pfannenstiel incision or an enlarged trocar incision. A surgical drain is placed near the pancreatic remnant. In the case of splenectomy this drain is placed via a long loop through the left upper quadrant with additional side holes to drain the splenic bed. The same approach can be followed with the DaVinci® console. Small variations according to the surgeon’s preference are allowed, but have to be recorded in the case report form.

### Control: open distal pancreatectomy

Patients undergo multimodal pain therapy with either an epidural catheter or wound catheters with patient-controlled analgesia [29]. Subcostal or midline laparotomy is performed. The steps taken are essentially similar to minimally invasive surgery but variation in technique is expected to be larger. In the case of benign or premalignant disease an attempt at splenic preservation is made, preferably using Kimura’s technique [26] (preservation of splenic vessels), but otherwise using Warshaw’s technique [27] (transecting splenic vessels). Tissue dissection during ODP, except for pancreatic transection, will be performed using a standardized ultrasonic device (Harmonic ACE® + 7 Shears, Ethicon Inc., Cincinnati, OH, USA, or similar device) within the LEOPARD trial. The pancreas is transected with a stapler. Alternatively, transection with ultrasonic devices, diathermia or sharp transection with suturing is allowed, as it is not expected that this will influence perioperative outcomes [30]. Additional suturing of the pancreatic stump, covering the stump with tissue or a patch, or staple-line reinforcement is allowed. Small variations according to the surgeon’s preference are allowed, but have to be recorded in the case report form.

### Conversion from MIDP to ODP

Conversion is defined as any MIDP (laparoscopic or robot-assisted) in which an incision is used for reasons other than trocar placement or specimen extraction. Patients allocated to MIDP who undergo intraoperative conversion to ODP will still be analyzed in the MIDP group according to intention-to-treat principles. Reasons for conversion will be registered.

### Patient blinding

Patients will be blinded using a large (30 × 30 cm) abdominal dressing, which is administered in the operating room immediately after the operation (Fig. 2). Patients are blinded until functional recovery has been reached or at least up to day 5 postoperatively. Earlier removal of the dressing is allowed for urgent medical reasons. Previous trials in The Netherlands have found this approach feasible [8, 31]. Full blinding of medical and nursing ward staff would include masking surgical notes to the hospital electronic patient system and is not considered feasible in all 17 centers.

**Fig. 2 Fig2:**
[figure not shown]
Abdominal dressing used to blind the patient for the type of distal pancreatectomy

### General treatment regimen

Postoperative care is similar in both arms and based on enhanced recovery after surgery principles, which include early mobilization and expanding oral intake as desired by the patient. When patients are functionally recovered, they are essentially medically ready to be discharged. The final date of discharge will be determined by the local treating team.

### Primary outcome

The primary outcome is time to functional recovery (days). Functional recovery will be daily assessed by the nurses, ward physicians and the trial coordinators and is reached when all of the following criteria are met:Adequate pain control with oral analgesia onlyRestoration of mobility to an independent level (or to preoperative level if previously impaired)Ability to maintain sufficient caloric intake (minimum of 50% required calories); absence of intravenous fluid administrationNo signs of active abdominal infection (in the case of abdominal infection this item is met when serum C-reactive protein is below 150 mg/L and the patient has no fever)

### Secondary outcomes

The secondary outcomes of this trial include operative outcomes (type of approach, vascular tumor involvement, tumor involvement in multiple organs, type of primary and secondary surgeon (resident, fellow or surgical specialist), conversion and reason for conversion, method of pancreatic transection, spleen preservation (including technique: Kimura/Warshaw), vessel resection, intraoperative blood transfusion, administration of somatostatin analogs, intra-operative complications, operative time (from first incision to full skin closure), total duration of the procedure and intraoperative blood loss, type of analgesia), postoperative outcomes (pain management, complications (e.g. postoperative pancreatic fistula, post-pancreatectomy hemorrhage, delayed gastric emptying and surgical site infection), postoperative intervention (radiologic, endoscopic, surgical), postoperative blood transfusion, intensive care unit admission, length of hospital stay, readmission, time to start adjuvant chemotherapy (in the case of malignant disease), mortality and Clavien-Dindo scores of all individual complications), pathology parameters (resected specimen length, tumor size, histopathological diagnosis, resection margins (including transection, anterior circumferential and posterior circumferential margins, in the case of malignancy), lymph node retrieval, tumor-positive lymph node retrieval (in the case of malignancy), neural and vascular tumor invasion), costs (intra-operative and postoperative costs) and quality of life.

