### Data collection and patient follow up

Baseline data (on age, sex, performance status (Karnofsky score), American Society of Anesthesiologists physical status, body mass index, malnutrition universal screening tool score (MUST), ERAS mobility scale [31, 32], diabetes mellitus, previous abdominal surgery, preoperative imaging including tumor size and involvement of other organs, preoperative diagnosis, indication for hospitalization, indication for surgery) will be collected before randomization using standardized case report forms. Data on the primary and secondary outcomes will be collected from randomization up to 90 days postoperatively, by the local treating physicians or the trial coordinators using standardized case report forms. The case report forms and the database will be crosschecked with source data by the trial coordinators.

Patients will be asked to complete validated questionnaires (EQ-5D-5 L and QLQ-C30) at 2 weeks, 4 weeks and 12 weeks postoperatively (Fig. 1). One year after surgery, patients will be asked whether they are totally recovered and will be asked to complete questionnaires on quality of life (Euro-QoL 5 health dimensions questionnaire (EQ-5D-5 L) and Quality of life questionnaire including 30 questions (QLQ-C30)), complications and whether they would recommend MIDP or ODP to a friend or family member. Long-term follow-up results of the LEOPARD trial (including complications and quality of life) will be published separately.

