### Statistical aspects

#### Sample size calculation

The LEOPARD trial is designed as a superiority trial, hypothesizing that the time to functional recovery is significantly shorter after MIDP compared with ODP. Based on the most recently published meta-analysis [11] and Dutch nationwide data, a time to functional recovery of 8 days in the control group (ODP) versus 6 days in the intervention group (MIDP) is expected with a standard deviation of 3 days. The significance level (α) is set at 0.05 and power (1-β) at 80%. The sample size needed in each arm, calculated using the independent samples *t* test, is 36 patients. Including 15% crossover from the MIDP to ODP and a rate of 2% loss to follow up (based on previous studies), a total of 51 patients will be randomized in each group, so a total of 102 patients will be randomized in the LEOPARD trial.

After completion of data collection in the first 75 patients, the data safety monitoring board will assess potential data skewness and homogeneity of variance for time to functional recovery. When a non-parametric test seems indicated for the comparison of MIDP versus ODP on time to functional recovery, the total sample size will become the calculated sample size (102) divided by the asymptomatic relative efficiency parameter of the Mann–Whitney *U* test (0.955). In that case, a total of 108 patients will be randomized in the LEOPARD trial. Procedures performed using the robot DaVinci® Surgical System are allowed in this trial, but will be analyzed separately during the cost analysis.

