#### Statistical analysis

Primary and secondary outcomes will be crosschecked with data from primary sources and a blinded adjudication committee will check them against the definitions, which were established before the start of this trial. Categorical variables will be compared using the chi-square or Fisher’s exact test as appropriate, and values will be expressed as proportions. The distribution of continuous variables will be determined using visual inspection and the Kolmogorov-Smirnov test.

For comparison of normally distributed continuous variables the independent samples *t* test will be used and values will be expressed as means with standard deviations. Continuous non-normally distributed variables will be compared using the Mann–Whitney *U* test and values will be expressed as medians with interquartile ranges. Measures of association will be expressed as relative risks with 95% confidence intervals. A difference with a two-tailed *P*-value <0.05 will be considered statistically significant.

Analyses will be performed based on intention-to-treat principles, meaning that converted MIDP will be assessed in the MIDP group. A multivariable linear regression model will be used to assess potential differences between groups in the primary outcome in the presence of potentially confounding factors. Linear mixed modeling will be applied to estimate differences between groups in successive EQ-5D-5 L and QLQ-C30 assessments over time. For exploratory purposes a secondary analysis will be performed comparing outcomes in patients with malignant versus non-malignant disease, comparing completed MIDP (i.e. no conversion) versus ODP and comparing time to functional recovery between MIDP and ODP in patients with complications (Clavien-Dindo score ≥ III) and without complications.

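### Time to start adjuvant chemotherapy falls under the generic t test or Mann-Whitney rule with data ending at day 90, so as written it in effect compares only patients who started by then

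*Protocol article*

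**What the plan says.** Four places in the protocol article bear on this point.

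- **Secondary outcomes** lists, among the postoperative outcomes, "time to start adjuvant chemotherapy (in the case of malignant disease"). It gives no starting point for the clock, no denominator and no rule for patients who do not start.
- **Data collection and patient follow up** sets the window: "Data on the primary and secondary outcomes will be collected from randomization up to 90 days postoperatively". The one-year contact described there covers recovery, quality of life, complications and whether the patient would recommend the operation. It does not mention chemotherapy.
- **Statistical analysis** gives the tests by type of variable: "For comparison of normally distributed continuous variables the independent samples *t* test will be used", and "Continuous non-normally distributed variables will be compared using the Mann–Whitney *U* test". Beyond these, it names linear regression for the primary outcome, linear mixed models for quality of life, and chi-square or Fisher tests for categorical variables, with relative risks and 95% confidence intervals as the measure of association. It also says: "Analyses will be performed based on intention-to-treat principles, meaning that converted MIDP will be assessed in the MIDP group".
- **Sample size calculation** shows that the article treats a time-to outcome as an ordinary continuous variable. The primary outcome is sized with a t test, and the sample size changes "When a non-parametric test seems indicated for the comparison of MIDP versus ODP on time to functional recovery".

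The article does not mention censoring, cumulative incidence, competing death, or a rank for patients without an event.

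**The concern.** A time to chemotherapy exists only for patients who receive chemotherapy, and under the stated window it is recorded only if that happens by day 90. A patient with cancer who dies, stays too unwell, or starts later has no number to enter. Unless a rule supplies one, the test runs on starters alone.

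Who becomes a starter is decided after randomization, partly by postoperative recovery, which is what the trial compares. If one operation lets slower-recovering patients start who would otherwise never start, they join that arm as late starters and lengthen its average. A benefit can then look like a delay, and a harm can be hidden in the same way. Intention to treat is spelled out only for conversions, so it does not settle how non-starters are handled.

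**Working it through.** **Plan's own figure.** There is none for this outcome. The stated sample size (36, inflated to 51 per arm) concerns the primary outcome. It matters here only because the patients with malignancy are some part of 51 per arm.

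**Assumptions (none of these is in the documents).** Early starters: 60% of each arm, day of start N(42, 10). Late starters: a further 20% with minimally invasive distal pancreatectomy (MIDP) only, N(72, 9). The rest never start. Data are cut at day 90. For simulation, 13 to 25 patients with malignancy per arm, which is 13/51 = 25% to 25/51 = 49%.

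**Step 1: late starters seen by day 90.** (90 − 72)/9 = 2, so the share seen is Φ(2) = 0.977. Their mean is 72 − 9 × φ(2)/Φ(2) = 72 − 9 × 0.0540/0.977 = 71.5 days.

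**Step 2: proportion started by day 90.** MIDP: 0.60 + 0.20 × 0.977 = 0.795. Open surgery (ODP): 0.60. The difference is about 20 points in favour of MIDP.

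**Step 3: mean among starters only.** MIDP: (0.60 × 42 + 0.195 × 71.5)/0.795 = 49.2 days. ODP: 42 days. MIDP looks about 7.2 days later.

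**Step 4: all patients, mean time truncated at day 90.**
- ODP: 0.60 × 42 + 0.40 × 90 = 61.2 days.
- MIDP: 0.60 × 42 + 0.20 × (0.977 × 71.5 + 0.023 × 90) + 0.20 × 90 = 57.6 days.
- MIDP is about 3.6 days shorter, so the sign has reversed.

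**Step 5: what Mann-Whitney estimates.** This is the chance that a random MIDP patient starts before a random ODP patient, counting ties as half. A late starter precedes an early one with probability Φ(−30/√(10² + 9²)) = Φ(−2.23) = 0.013.
- Starters only: (0.60/0.795) × 0.5 + (0.195/0.795) × 0.013 = 0.38, against MIDP.
- Everyone, with non-starters sharing the worst rank: 0.6 × 0.6 × 0.5 + 0.6 × 0.4 + 0.195 × 0.6 × 0.013 + 0.195 × 0.4 + 0.205 × 0.4 × 0.5 = 0.54, for MIDP.

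**Step 6: simulation, 4,000 trials per setting.**

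| Setting | Starters-only mean difference | Starters-only median difference | Starters-only Mann-Whitney P<0.05 | Worst-rank Mann-Whitney points to MIDP |
|---|---|---|---|---|
| 60% + 20%, 13 per arm | about +7.2 days | about +4.9 days | 10% to 12% | about 65% |
| 60% + 20%, 25 per arm | about +7.2 days | about +4.5 days | about 20% | about 69% |
| Equal starting, both sizes | 0 | 0 | about 5% | about 50% |

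With worst ranks, significance against MIDP occurs in about 1% of trials in the 60% + 20% setting.

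**Sensitivity.** With a further 10% in place of 20%, Step 3 gives (25.2 + 0.0977 × 71.5)/0.698 = 46.1, or +4.1 days. A separate set of assumptions has half of each arm starting near day 45 and slow starters near day 80. Its slow shares are 30% MIDP and 10% ODP, and its never-starting shares are 20% and 40%. It gives 53.9 versus 48.8 days among starters (+5.1) and 63.8 versus 66.3 days in all patients truncated at day 90 (−2.5).

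**The case against.** The strongest reply is that the article never says non-starters are dropped. It lists the outcome, gives a generic rule by variable type and affirms intention to treat. A full protocol or analysis plan could add a censoring or ranking rule, and such detail is often left there. This stands in part: exclusion is implied by the text and not stated. But the article does fix a rule for continuous variables, handles its primary time-to outcome under that rule, and closes data collection at day 90. Followed literally, these lead most naturally to a starters-only comparison. The point therefore concerns a stated choice that suits this outcome badly, and is more than a request for missing detail.

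Three stronger readings are tempting, and the documents do not support them:

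- **That non-starters cannot enter either test.** This is wrong for Mann-Whitney, which needs only ranks. With a common cut-off at day 90, non-starters can share the worst rank. Step 5 shows that the direction is then right in the illustration. The fault lies in having no rule for non-starters, not in the rank test itself.
- **That the result will reverse.** Reversal depends on unequal starting between arms, which the illustration assumes. With equal starting the bias is zero. Even in the illustration, roughly 80% to 90% of trials show no significant starters-only difference.
- **That this is the outcome that matters most to patients with cancer.** The article does not rank it above mortality, resection margins or lymph node retrieval.

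**Conclusion.** The point holds as a minor correction to one secondary outcome. Under the stated tests and window, and with no value or rank for patients who have not started, the comparison is in effect limited to starters by day 90 and departs from the stated intention-to-treat principle. The starters-only difference is biased if the proportion starting differs between arms, and it can then take the wrong sign: about +7 days against an arm in which about 20 points more patients start, or about +4 days with a 10-point gain. These sizes rest wholly on assumed start rates, start times and subgroup sizes. They show what is possible and do not predict what will happen. The primary outcome and the sample size are untouched.

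**What to change.** Add an analysis rule for this outcome:

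- **Denominator, stated in advance.** All randomized patients with confirmed malignancy of a type for which adjuvant chemotherapy is indicated, whether or not the patient was fit to receive it. Without this, patients who would never be offered chemotherapy count as non-starters. It would also stay open whether malignant means the indication at randomization or the final pathology.
- **Main analysis.** Time from surgery to first adjuvant chemotherapy as a time-to-event outcome, censored at day 90, with death as a competing event. Show cumulative incidence by arm, and report the proportion started by day 90 with a relative risk and 95% confidence interval, a measure the article already uses.
- **Simpler alternative.** A Mann-Whitney test in the same denominator, with all patients not started by day 90 given the worst tied rank.
- **Starters-only times.** Report them as descriptive, if at all.

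The cost is a few lines of analysis wording and a little programming. Time to start chemotherapy, mortality and histopathological diagnosis are already listed outcomes, so little or no new data collection is needed. The downside is a wide interval, because the subgroup is small.
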